
## 9.4. Study specimen and procedure management

Planned analysis of circulating and other biomarkers will be determined by specialized laboratories/departments as outlined below:

| **Specimen (amount)** | **Laboratory** |
| --- | --- |

| **Serum: 6 aliquots (2 mL each) per time point**  For all circulating biomarkers  At baseline, 3 months, and 6 months (or study cessation) | [name], PhD  Division of Cancer Prevention and Genetics  European Institute of Oncology |
| --- | --- |
| **Stool: 1 aliquot per time point**  Microbiota analysis at baseline and 6 months  **Whole blood 1 aliquot per time point**  Immune-gene expression profile | Istituto Nazionale Tumori G. Pascale, Naples |
| **Mammograms***  Baseline and final images will be recorded to mammographic analysis | [name] MD  Department of Breast Radiology,  European Institute of Oncology |

*Only in a subgroup of participants

## 9.5 Shipping Instructions

In order to keep shipping costs at an affordable level, Participating Centers are requested to store blood and stool samples at -80°C. Dry-ice shipment of serum and blood samples will be arranged by the Lab at the Division of Cancer Prevention and Genetics, European Institute of Oncology in Milan. Storage of serum and blood samples will be centralized at the same Laboratory. Dedicated lab staff will provide kits for sample collection, will be in charge of sample identification and database implementation at arrival and the will coordinate the shipment of samples to the specific laboratories involved in biomarker measurements (i.e., Istituto Nazionale Tumori IRCCS Fondazione G. Pascale Napoli).

Contact:

Division of Cancer Prevention and Genetics

European Institute of Oncology

[name]

[name]

[name]

[contact]

E-mail address: [[contact]](mailto:[contact])

# 9.6 Specimen Banking

If the participant gives her consent, leftover specimens from the laboratory work will be stored at ieo biobank for future research studies on breast cancer prevention. Contrarily, the specimens will be destroyed after study completion. The biobank will store the specimens until depleted, and anyhow no longer than 25 years from collection. The donor will be re-contacted to give a new consent for the future use of leftover samples. In the event of a future secondary use, the study will be evaluated by the ethic committee.

# 10. REPORTING ADVERSE EVENTS (AE)

DEFINITION: AE means any untoward medical occurrence associated with the use of a drug in humans, whether or not considered drug related. An AE can therefore be any unfavorable and unintended sign, symptom, or disease temporally associated with participation in a study, whether or not related to that participation. This includes all deaths that occur while a participant is on a study.

Please note that all abnormal clinical laboratory values that are determined to be of clinical significance based on a physician’s assessment are to be reported as AEs. Those labs determined to be of no clinical significance or of unknown clinical significance (per the physician’s assessment) should not be reported as AEs. Any lab value of unknown clinical significance should continue to be investigated/followed-up further for a final determination, if possible.

A list of AEs that have occurred or might occur (Reported Adverse Events and Potential Risks) can be found in §6.2, Pharmaceutical Information, as well as in the Summary of Product Characteristics.

## 10.1 Adverse Events

Reportable AEs

All AEs that occur after the informed consent is signed and baseline assessments are completed must be recorded on the AE CRF (paper and/or electronic) whether or not related to study agent.

Cases of overdose, medication error, drug abuse, or drug misuse, along with any associated adverse events, should be reported.

AE Data Elements:

The following data elements are required for adverse event reporting.

- AE verbatim term
- NCI Common Terminology Criteria for Adverse Events version 6.0 (CTCAE v 5.0) AE term (MedDRA lowest level term)
- CTCAE (MedDRA) System Organ Class (SOC)
- Event onset date and event ended date
- Treatment assignment code (TAC) at time of AE onset
- Severity grade
- Attribution to study agent (relatedness)
- Whether or not the event was reported as a serious adverse event (SAE)
- Whether or not the subject dropped due to the event
- Outcome of the event

Severity of AEs

Identify the AE using the CTCAE v 5.0. The CTCAE provides descriptive terminology (MedDRA lowest level term) and a grading scale for each AE listed. A copy of the CTCAE can be found at:

https://ctep.cancer.gov/protocolDevelopment/electronic_applications/docs/CTCAE_v5_Quick_Reference_5x7.pdf

AEs will be assessed according to the grade associated with the CTCAE term. AEs that do not have a corresponding CTCAE term will be assessed according to the general guidelines for grading used in the CTCAE v5.0 as stated below.

**CTCAE v5.0 general severity guidelines:**

| Grade | Severity | Description |
| --- | --- | --- |
| 1 | Mild | Mild; asymptomatic or mild symptoms; clinical or diagnostic observations only; intervention not indicated. |
| 2 | Moderate | Moderate; minimal, local or noninvasive intervention indicated;  limiting age-appropriate instrumental activities of daily living (ADL)*. |
| 3 | Severe | Severe or medically significant but not immediately life-threatening;  hospitalization or prolongation of hospitalization indicated; disabling; limiting self-care ADL**. |
| 4 | Life-threatening | Life-threatening consequences; urgent intervention indicated. |
| 5 | Fatal | Death related to AE. |

* **ADL**

*Instrumental ADL refers to preparing meals, shopping for groceries or clothes, using the telephone, managing money, *etc*.

**Self-care ADL refers to bathing, dressing and undressing, feeding self, using the toilet, taking medications, and not bedridden.

Assessment of relationship of AE to intervention

The possibility that the adverse event is related to intervention will be classified as one of the following: not related, unlikely, possible, probable, definite.

Adverse events potentially related to tamoxifen treatment have been described in section 6.2 and are available in the SmPC of tamoxifen.

Fasting and intermittent fasting have been reported to cause some adverse events such as feeling cold, lack of energy, and occasional dizziness, nausea, insomnia, syncope, falls, migraine headache, weakness that limits daily activities, and excessive hunger pangs^64, 65^. We do not foresee any serious adverse event. However, if participants will experience an adverse event, this will be reported immediately to the attention of the clinical staff. All participants will be monitored to prevent any possible deficiency, dehydration or inadequate nutrient and/or caloric intake by means of an evaluation of their dietary intake. Participants will also be monitored for injuries or problems associated with the increased physical activity.

Participants are invited to contact the clinical sites to report any AE for clinical evaluation and management.

Follow-up of AEs

All AEs, including lab abnormalities that in the opinion of the investigator are clinically significant, will be followed according to good medical practices and documented as such.

## 10.2 Serious Adverse Events

Definition of SAE

Serious adverse event (SAE) is defined as one of the following:

Is fatal or life-threatening

Results in persistent or significant disability/incapacity

Constitutes a congenital anomaly/birth defect

Is medically significant, i.e., defined as an event that jeopardizes the patient or may require medical or surgical intervention to prevent one of the outcomes listed above

Requires inpatient hospitalization or prolongation of existing hospitalization.

Note that hospitalizations for the following reasons should not be reported as serious adverse events:

Routine treatment or monitoring of the studied indication, not associated with any deterioration in condition (i.e. to perform study related assessments)

Elective or pre-planned treatment for a pre-existing condition that is unrelated to the indication under study and has not worsened since signing the informed consent

Social reasons and respite care in the absence of any deterioration in the patient’s general condition

Note that treatment on an emergency outpatient basis that does not result in hospital admission and involves an event not fulfilling any of the definitions of a SAE given above is not a serious adverse event

Reporting

To ensure patient safety every SAE, regardless of suspected causality, occurring after the patient has provided informed consent and until at least 30 days after the patient has stopped study treatment must be reported to the EIO Pharmacy within 24 hours of learning of its occurrence.

Any additional information for the SAE including complications, progression of the initial SAE, and recurrent episodes must be reported as follow-up to the original episode within 24 hours of the investigator receiving the follow-up information. A SAE occurring at a different time interval or otherwise considered completely unrelated to a previously reported one should be reported separately as a new event.

Any SAEs experienced after the 30-day safety evaluation follow-up period should only be reported to the EIO Pharmacy if the investigator suspects a causal relationship to the study treatment.

Information about all SAEs is collected and recorded on the Adverse Event Report Form; all applicable sections of the form must be completed to provide a clinically thorough report. The Investigator must assess and record the relationship of each SAE to each specific study treatment (if there is more than one study treatment), complete the AE Report Form in English, and submit the completed form within 24 hours to EIO Pharmacy.

Follow-up information is submitted in the same way as the original AE Report. Each reoccurrence, complication, or progression of the original event should be reported as a follow-up to that event regardless of when it occurs. The follow-up information should describe whether the event has resolved or continues, if and how it was treated, whether the blind was broken or not (if applicable), and whether the patient continued or withdrew from study participation.

If the SAE is not previously documented in the Investigator’s Brochure or Drug Package Insert (new occurrence) and is thought to be related to the study treatment, the Safety Committee of EIO may urgently require further information from the investigator for Health Authority reporting. Suspected Unexpected Serious Adverse Reactions (SUSARs) will be collected and reported to the Competent Authorities and relevant Ethics Committees in accordance with applicable national regulatory requirements.

Pregnancies

Should pregnancy occur, to ensure patient safety, each event must be reported to the EIO Pharmacy within 24 hours of learning of its occurrence.

The pregnancy should be followed up to determine outcome, including spontaneous or voluntary termination, details of the birth, and the presence or absence of any birth defects, congenital abnormalities, or maternal and/or newborn complications.

Pregnancy follow-up should be recorded on the same form and should include an assessment of the possible relationship to the study treatment any pregnancy outcome. Any AE experienced during pregnancy must be reported on the AE Report Form.

The Study Doctor will collect information such as progression of the pregnancy, the pregnancy outcome and the health of the baby. The collection of this information could last for up to 3 months following the birth of the child, and longer if required by the Safety Committee. Consent to report information regarding these pregnancy outcomes should be obtained from the mother.

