**Phone call/ teleconsulting (at 5 months) (T5)**

**Final clinical visits (T6)**

Physical exam, toxicity assessment, concomitant medications, fasting blood and stool collection for clinical lab tests and biomarkers, self-reported questionnaires, compliance/review pill diary.

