## 2.3 Schedule and duration of intervention

Duration of intervention: Phase II studies have the advantage to be able to reach their endpoint in a short period of time. Drugs biological effect can be seen within days if not hours. SHBG modulation by tamoxifen can be seen already at two weeks as reported by Birzniece et al. ^47^. Their paper showed a significant SHBG increase for both 10 and 20 mg already after two weeks of treatment. Our presurgical study reported specifically for 5 mg per day of tamoxifen a modulation of SHBG from nmol/L 65.3 (52.5 to 78.1) to 70.9 (60.2 to 81.7) in four weeks (significant trend compared with the control arm) ^5^.

We have published a paper with tamoxifen a 10 mg a week where the increment of SHBG was seen at three months and was stable at six and 12 months (published data on the ratio Estradiol/SHBG, row for SHBG data alone not published) ^48^. Finally, a subsequent prevention study with low dose tamoxifen measured SHBG only at 12 months ^17^. With all these observations we decided to set at six month our intervention, sufficient to see the modulation of the primary endpoint but also useful to see effects of the LI and ICR arms and quality of life.

Drug schedule: Our main randomized trial used a non-commercially available formulation of 5 mg per day. Tamoxifen has a long half-life^49^, and we explored also lower dose likewise 1 mg per day and 10 mg per week^48, 50^. All these lower doses/schedules have shown that tamoxifen maintains biological effects, including SHBG modulation^48^. Furthermore, this specific schedule has been already used for intraepithelial patients with a clinical benefit decrease by 30% of new breast events (either in situ or invasive)^6^. To have a pragmatic approach and to reduce expenses we choose the commercially available dose of 10 mg every other day (equivalent to 5 mg per day) to avoid a study-specific drug formulation.

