# 3. STUDY DESIGN

The TOLERANT (Low dose **T**am**O**xifen and **L**if**E**style changes for b**R**east c**AN**cer preven**T**ion) study is a randomized four-arm phase II intervention trial that will enroll 200 participants at high risk of breast cancer in four Italian centers (Milan, Genoa, Padua and Naples).

Potentially eligible women will be informed about the study and will provide signed informed consent before participation. At baseline, participants will be screened to confirm eligibility and will be randomly assigned (1:1:1:1) to one of the four intervention arms (Figure 1):

*Arm 1:* Low dose Tamoxifen (LDT) i.e 10 mg every other day;

*Arm 2:* Low dose Tamoxifen (LDT) + Intermittent Caloric Restriction (ICR);

*Arm 3:* Lifestyle intervention (LI) using a step counter;

*Arm 4:* Lifestyle intervention (LI) using a step counter + Intermittent Caloric Restriction (ICR).

Figure 1

[figure not shown]

Stratification: center and disease status (high risk vs previous IEN)

A schematic description of the study procedures is reported in figure 2.

Figure 2

[figure not shown]

Trained staff including dietitians/nutritionists will provide advices based on international and national recommendations (WCRF.2018; CREA, 2019 https://www.crea.gov.it/web/alimenti-e-nutrizione/-/linee-guida-per-una-sana-alimentazione-2018) at baseline to all participants. Depending on intervention allocation, dietitians/nutritionists will provide a caloric restriction plan to Arm 2 and 4. Participants included in Arm 3 and 4, will receive a step counter that encourages both increased physical activity and decreased sedentary time. Depending on intervention allocation, tamoxifen pills will be provided (Arm 1 and 2). All participants will receive a calendar in order to record drug intake, ICR dates and weekly step counter where appropriate. The study interventions will last 6 months.

To maintain high compliance during the 6-month intervention phase (T2, T3 and T5) participants will receive phone calls in order to monitor and reinforce adherence to the proposed intervention, and to record possible adverse effects. At visit T1, T4 and T6 blood samples will be collected, anthropometric measures, study questionnaires will be collected. Stool will be collected at T1 and T6. Depending on local availability, a sub-sample of participants will be invited to do DEXA for adipose tissue evaluation.

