## 7.8 Off-Study Criteria

Participants may go ‘off-study’ for the following reasons: the protocol intervention and any protocol-required follow-up period is completed, adverse event/serious adverse event, lost to follow-up, non-compliance, concomitant medication, medical contraindication, withdrawn consent, death, determination of ineligibility (including screen failure)*.*

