## 7.9 Study termination

Primary completion date will be the date that the last participant will undergo the final visit for the purpose of final collection of data for the primary outcome.

Study completion date will be the final date in which all secondary endpoints will be assessed.

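### No scheduled contact covers the 30-day post-treatment SAE window that protocol section 10.2 sets, because the schedule of events ends at T6

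*Protocol*

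**What the plan says.** Section 10.2 sets the reporting rule. Every SAE, whatever its cause, from consent onward, "until at least 30 days after the patient has stopped study treatment must be reported to the EIO Pharmacy within 24 hours of learning of" it. The section then changes the rule at the end of those 30 days: "Any SAEs experienced after the 30-day safety evaluation follow-up period should only be reported to the EIO Pharmacy" when a causal link to study treatment is suspected. The 30 days are therefore named as a study period, and their end decides which events must be reported.

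The visit plan is in sections 3 and 7. Section 3 states: "The study interventions will last 6 months". The schedule of events in 7.1 runs from T0 to T6, and its adverse-event row ends at T6, the final visit at 6 months. Section 7.4 places telephone contacts at T2, T3 and T5 only. Section 7.6 has the study drug collected at the final visit.

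Section 7.8 allows a woman to go off study when "the protocol intervention and any protocol-required follow-up period is completed", but no section says what that follow-up period is. Section 7.9 ties primary completion to T6: "Primary completion date will be the date that the last participant will undergo the final visit".

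**The concern.** Section 10.2 names a safety follow-up period that the visit plan does not contain. A site working from the schedule has no prompt to contact a completer after T6, no adverse-event entry to fill in for the following 30 days, and no defined follow-up to finish before applying section 7.8. It learns of a later SAE only if the woman, or someone else, reports it.

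Safety and toxicity is a secondary endpoint (8.2), and section 8.2 has it evaluated at the clinical visit; no clinical visit falls in these 30 days. The protocol's own background gives reasons to look there. Section 2 lists venous thromboembolic events among the toxicities of tamoxifen, and section 2.3 says "Tamoxifen has a long half-life". At stake is whether the count of SAEs in the stated window is complete.

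**Working it through.** The plan gives no figure for this point, so the check compares the SAE window with the scheduled contacts and then sizes the gap.

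**Inputs**
- SAE window: consent to at least 30 days after study treatment stops (10.2).
- Length of intervention: 6 months (3, 5.1), about 183 days.
- Scheduled contacts after randomization: T2 (within 1 month), T3 (2 months), T4 (3 months), T5 (5 months), T6 (6 months) (7.1).
- Tablets collected at T6 (7.6), so treatment ends at or about T6 for a completer.
- Enrolment 200, drop-out allowance 10% (12.1).

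**Completers**
- Treatment ends at about day 183. The window runs to about day 183 + 30 = 213.
- Scheduled contacts after day 183 and up to day 213: 0.
- Post-treatment days covered by a planned contact: 0 of 30.
- Share of the on-treatment-plus-30-day window: 30 / (183 + 30) = 30 / 213 = 14.1%.

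**Women who stop early**
- T6 falls at least 30 days after stopping only if the woman stops by about day 183 − 30 = 153, which is roughly month 5.
- A woman who stops later has T6 inside her 30 days. The remainder of her window, after T6, has no planned contact.
- Even for earlier stoppers the cover is conditional. Section 7.7 continues follow-up where possible, and section 7.8 lets women leave the study for reasons such as an adverse event, non-compliance or withdrawn consent.

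**Number of women**
- Expected completers: 200 × (1 − 0.10) = 180.
- With 1:1:1:1 allocation, about 180 / 2 = 90 of them are in the two tamoxifen arms.

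**Other routes in the text**
- Section 10.1 invites participants to contact the site about any AE and gives no end date. This is a spontaneous route.
- Section 7.1, note c, allows a mammogram within 6 or 12 months of baseline in a subgroup. It is imaging, is not tied to day 30 and is not described as a safety contact.
- Section 10.2 follows a pregnancy once it is known. It schedules no contact at which a pregnancy would be asked about.

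None of these is a planned SAE enquiry within the 30 days.

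**The case against.** The strongest reply is that section 10.2 creates a duty that starts when the site becomes aware of an event. Such a duty can coexist with a schedule that has no day-30 contact, so the two sections differ only in that the method of ascertainment is unstated. Section 10.1 keeps a reporting route open, some participants are mutation carriers already followed in the centers' clinics, and section 7.8 read together with 10.2 might be taken to include the 30 days. A sentence saying that the period relies on spontaneous reports would also reconcile the text.

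Much of this stands. The window is not unobserved; it is not actively ascertained. The protocol requires reporting on awareness and nowhere promises active collection to day 30. What remains is that section 10.2 calls the 30 days a safety evaluation follow-up period, while the schedule provides no evaluation in it and 7.8 does not identify it.

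A reader might infer that tamoxifen's safety result would look cleaner than it should. The documents do not support that. The gap after T6 is the same in all four arms, and no difference in spontaneous reporting between arms is shown. Section 2 also reports no excess of thromboembolic events or endometrial cancer with low-dose tamoxifen in the earlier phase III trial, and section 2.4 expects few adverse events.

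A reader might also infer that completers are missed and early stoppers are covered. That contrast is not absolute, given sections 7.7 and 7.8 and the women who stop in the last month. Finally, 14.1% is a share of calendar days, not of SAEs.

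**Conclusion.** The point holds as a mismatch between section 10.2 and sections 7.1 and 7.8. For completers the last scheduled contact coincides with the end of treatment, and all 30 post-treatment days depend on spontaneous reports. For women who stop in the last month, the same is true of the days after T6. Under-counting of SAEs in that time is possible; its size, and any difference between arms, cannot be established from the protocol.

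The figure of about 180 women assumes that the 10% sample-size allowance describes actual drop-out. The statement that treatment ends at T6 rests on the 6-month duration and on the return of tablets at that visit. For the lifestyle arms, the end of study treatment is read as the last day of the assigned intervention. Randomization, power and the primary SHBG comparison are unaffected. The change should be made because the window is already stated and the remedy is cheap.

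**What to change.** Add one telephone contact to the schedule of events in 7.1, in all four arms, at or just after 30 days from the last dose or last day of intervention. Ask about SAEs, unresolved AEs and pregnancy. Name this contact in 7.8 as the protocol-required follow-up, and refer to it in 10.2 as the end of the 30-day period. If the sponsor prefers not to add a contact, 10.2 should at least say that the period relies on spontaneous reports, so that the SAE counts are read accordingly; that reconciles the text but does not improve ascertainment.

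The cost is one short call per participant, which can be made by the staff who already make the T2, T3 and T5 calls, and one eCRF page. The last safety contact falls about one month later than now. The primary completion date in 7.9 stays at T6.
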